## Abstract

**Background:**

Pressure ulcers (PUs) on the buttocks are among the most common secondary complications in individuals with chronic spinal cord injury (SCI). PUs can result from sitting for extended periods, disuse atrophy, increased sitting pressure and reduced circulation. Compared with usual care, activation of paralysed muscles using electrical stimulation (ES) has been shown to markedly increase paralysed muscle mass, improve circulation of skin and muscle and improve sitting pressure distribution. ES might therefore be a useful method to reduce PU incidence.

**Methods:**

A multicentre randomized controlled trial (SCI PREVOLT) will be conducted with an economic and process evaluation alongside. One hundred participants with a SCI in the chronic phase and a minimal incidence of 1 PU in the last 5 years will be recruited from rehabilitation centres across the Netherlands. Participants will be stratified by centre and age and randomized to the intervention or control group. The intervention group will use ES at least 1 h/day during at least 4 times a week for 1 year next to usual care. The control group will only receive usual care. The primary outcome is the incidence of PUs, measured by a blinded person assessing the presence or absence of a PU on the buttocks on a photo made by the participant or his/her caregiver. The incidence of a PU will be evaluated every 2 weeks. Secondary outcomes include interface pressure distribution, blood flow in the profunda femoris artery, muscle thickness of the hamstrings and gluteal muscles and questionnaires about different dimensions of life, e.g. participation and quality of life. Secondary outcomes will be measured at baseline and 3, 6, 9 and 12 months after randomization.

**Discussion:**

This study will assess if electrical stimulation is a (cost-)effective method to prevent PUs and reduce the risk factors of getting PUs. If ES is effective and cost-effective compared with usual care, ES could be implemented in daily treatment of individuals with a SCI.

**Trial registration:**

Netherlands Trials Register NTR NL9469. Registered on 26 May 2021.

**Supplementary Information:**

The online version contains supplementary material available at 10.1186/s13063-022-06088-0.

## Introduction

### Background and rationale {6a}

Pressure ulcers (PUs), a common secondary complication in individuals with spinal cord injury (SCI), are characterized by damage to the skin and/or underlying tissue due to unrelieved pressure or pressure in combination with shear forces [1]. PUs develop following a prolonged period of compression and usually occur over bony prominences [2–6]. This compression of the tissue between a bony prominence, the skin and a surface, causes in turn the occlusion of capillaries leading to tissue ischemia and necrosis [7–9]. In severe cases, PUs can even be life-threatening [10–12].

Individuals with SCI are at an increased risk of developing PUs due to factors, such as reduced mobility, inability to adequately release pressure, atrophy of the paralysed muscles, a disturbed leg muscle pump function, reduced microcirculation and impaired sympathetic function [13]. Up to 85% of all individuals with SCI develop a pressure ulcer (PU) once or more in their life [6, 14–16]. A Dutch multicentre study found the occurrence of PUs during inpatient rehabilitation to be 37–39% [17]. Results of Adriaansen et al. [18] showed that the prevalence of a PU was 42%, 41% and 29% among individuals with SCI, 1, 2 and 5 years respectively after discharge. Two other studies found the overall PU incidence was still 29% after 10 years for individuals living with SCI [19, 20]. Many individuals with SCI suffer from recurrent PUs (> 1 every 3 years), with 40–80% of those who develop a PU having at least one recurrence [12]. Verschueren et al. [17] showed that having had a PU during the acute rehabilitation phase was the strongest predictor for a recurrence.

Usual PU preventive care starts during inpatient rehabilitation on a specialized SCI unit and follows the multidisciplinary guideline “Decubitus preventie en – Behandeling” [21], the Dutch translation of the international guidelines of the National and European Pressure Ulcer Advisory Panel [22]. This guideline consists of advice on choosing an adequate wheelchair, anti-PU cushion, lifestyle and nutrition, pressure-relieving movements, training how to perform adequate transfers, visually skin condition self-checks and psychosocial therapy, if needed. However, these methods do not meet the demands necessary for adequate management and prevention of PUs [1].

#### Relevance

After being diagnosed with a PU, treatment can either be conservative or surgical (debridement) and reconstructive and very often consists of mandatory prolonged bed rest to release pressure on the wound(s). Even though bed rest alleviates pressure on the wound, it also has some severe negative consequences, such as decreased mobility and independence and reduced physical condition, health-related quality of life and level of participation. On top of that, PUs are associated with high societal costs due to increased health care utilization and work absenteeism [2, 3, 23]. Consequently, preventing the recurrence of PUs will likely lead to a reduction of the burden to individuals with SCI and society.

#### Electrical stimulation

A method to potentially prevent the recurrence of PU is activating the paralysed muscles using electrical stimulation (ES). ES has been found to markedly improve PU risk factors by improving paralysed muscle mass and local circulation of skin and muscle [6, 24–30]. However, randomized controlled trials (RCTs) to confirm the effect of ES on reduction of PU recurrence are lacking and the cost-effectiveness of ES in individuals with SCI is unknown. Even though ES is not a new intervention, it has not yet been implemented widely in clinical SCI rehabilitation practice, largely due to the lack of well-controlled studies.

#### Existing evidence of the effectiveness of electrical stimulation

Preliminary studies found that intermittently activating the gluteal muscles during 30 min using surface ES acutely reduced interface pressures [31]. Studies also showed positive results in a reduction of interface pressure and blood flow restoration when performing ES on the gluteal and hamstring muscles. This was performed for a longer stimulation period (3 h) in a more daily-life situation in which participants wore a lycra garment with built-in electrodes and used a portable stimulator [32–35]. More recently, Barton et al. [36] performed a study involving nine individuals with a chronic SCI, who performed 12 weeks of a self-administered and self-chosen daily gluteal and hamstring stimulation, which showed that ES results in transduced structural and functional changes in the femoral artery supplying the active skeletal muscle, an improved sitting pressure distribution, an increased muscle mass and a moderately improved cutaneous microvascular function at the gluteal site.

In summary, ES seems promising in reducing potential risk factors of developing recurrent PU or a PU itself. However, a study evaluating the effect of ES as a preventive method for PUs is missing in the literature. Therefore, an RCT is needed to assess the effectiveness and cost-effectiveness of electrical stimulation plus usual care on the occurrence of PUs compared with only usual care.

### Objectives {7}

#### Primary objective

To investigate whether daily ES of gluteal and hamstring muscles combined with usual care is more effective in reducing recurrences of PUs than only usual care in individuals with chronic SCI, who had minimally 1 PU within the last 5 years.

#### Secondary objective(s)

To investigate whether daily electrical stimulation of gluteal and hamstring muscles combined with usual care is more effective than usual care only in improving:Factors related to PU risk: interface pressure distribution, local circulation and muscle size;Mobility, participation and quality of life;

In individuals with chronic SCI, who had minimally 1 PU within the last 5 years.
2.To determine the cost-effectiveness of ES compared with usual care alone.3.To investigate facilitators and barriers for the implementation and sustainability of daily ES of gluteal and hamstring muscles combined with usual care.4.To evaluate the usability and user-friendliness of the ES system.

### Trial design {8}

A prospective multicentre RCT will be conducted with an economic and process evaluation alongside. One hundred participants with a chronic SCI will be randomly assigned to either an intervention or control group. It is a superiority trial that aims to evaluate whether daily ES (intervention group) is more effective than usual care (control group) on the prevention of pressure ulcers.

## Methods: participants, interventions and outcomes

### Study setting {9}

The aim is to carry out this study in all eight Dutch rehabilitation centres with a specialized SCI unit: Reade centre for rehabilitation and rheumatology, location Overtoom, located in Amsterdam, Adelante located in Hoensbroek, Heliomare located in Wijk aan Zee, de Hoogstraat rehabilitation located in Utrecht, Roessingh located in Enschede, Rijndam located at Rotterdam, Sint Maartenskliniek located in Nijmegen and UMCG, location Beatrixoord, located in Haren.

### Eligibility criteria {10}

#### Inclusion criteria

To be eligible for this study, an individual must meet all of the following criteria:
Individuals with either a complete (AIS A) or incomplete (AIS B, C and D) chronic SCI^1^Age 18 years and olderIntact gluteal and hamstring muscles^2^A minimal incidence of 1 PU or more of category II-IV in the sacral or ischial tuberosity’s region within the last 5 years^3^Able to lie in a prone position for at least 10 min (safely for the neck, comfortable, not compromising breathing and taking possible contractures into account)

#### Exclusion criteria

Exclusion criteria are:
Current PUs in the gluteal or sacral areaFlaccid paralysis (areflexia)A history of severe autonomic dysreflexiaInsufficient mastery of the Dutch language (speaking and reading)Severe cognitive or communicative disordersIntolerance to or contra-indication for ES (cancer, pregnant)Recent or current participation in an ES-induced exercise program or study (up to 6 months prior to this study)Severe psychiatric illness or disorders (to the discretion of the treating rehabilitation physician)

### Recruitment {15}

Participant recruitment will occur between Start in May 2021 for approximately 1 year. Recruitment consists of approaching a potential participant in two different ways, i.e. active and inactive recruitment.

For the active recruitment strategy, rehabilitation physicians, Physician Assistants (PA), wound nurse and interns will distribute flyers and the information letter among individuals who may qualify for the study. Both will be distributed during a discharge interview, an outpatient appointment or at the patient’s follow-up interview 1 year after discharge. If a potential participant immediately expresses his/her interest in participating in the study, the practitioner will ask for permission to pass on his/her contact details (name and telephone number) directly to the local research assistant. The practitioner will then inform the patient that this local appointed and trained research assistant will contact them by telephone to make an appointment for the physical screening to check for eligibility. So, in the case of active recruitment, there will be no telephone pre-screening because the practitioners will only hand out flyers to potential participants who they regard will (at least) partially meet the inclusion and exclusion criteria.

For the inactive recruitment strategy, flyers will be distributed within the eight Dutch SCI rehabilitation centres and within the network of the Dutch SCI patient organization (Dwarslaesie Organisatie Nederland (DON)). Within the DON, the flyer will be distributed via social media and the flyer will be published in their magazine. When someone is interested in participating, he/she can contact the executive or principal investigator directly by email or telephone, using the contact details provided in the flyer. The executive or principal investigator will then perform a pre-screening interview via telephone. A telephone pre-screening interview is chosen in order to not unnecessarily burden potential participants with a visit to the rehabilitation centre. During this pre-screening, a brief explanation is given about the research. Subsequently, permission is asked to ask questions about the health of the potential participant in order to assess whether someone is suitable for study inclusion. If someone meets these written inclusion and exclusion criteria, permission is again requested to pass on the contact details to a local research assistant. The local research assistant from the nearest rehabilitation centre will make an appointment with the potential participant for the physical screening and will send the information letter via email prior to the screening (at least 5 working days due to the reflection time).

### Who will take informed consent? {26a}

The physical screening is carried out by the local investigator or trained research assistants and consists of reassessment of the inclusion and exclusion criteria, an extensive oral explanation of the research study and the opportunity to ask questions. If someone agrees to participate, the informed consent will be signed in duplicate. After this, the physical inclusion or exclusion criteria will also be assessed, namely the contraction of the hamstring and gluteal musculature. If these inclusion criteria have also been met, the participant will be included in the study. After the baseline questionnaire is fully completed, the participant will be randomized to the intervention or control group. For the informed consent, see Appendix 2.

## Assignment of interventions: allocation

### Implementation {16c}

#### Sequence generation {16a}

Randomization will be done by the research assistant of Reade. Participants will be randomly assigned to either the intervention or control group in a 1:1 ratio with a web-based randomization program (studyrandomizer.com). A permuted block algorithm will be used with a variable block size with a minimum of 4, a maximum of 8 and an increment of 2. Randomization will be stratified for rehabilitation centre and for two age groups; i.e. 18–70 years and ≥70 years. Randomization list will only be available to the local researcher of the rehabilitation centre, the executive investigator and principal investigator. The research assistant of Reade is also the one who completes the Case Report Form (CRF) and keeps everyone posted on how many participants are enrolled to the study.

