#### Concealment mechanism {16b}

Participants will be randomized using the program Study Randomizer (studyrandomizer.com), which is a web-based randomization service. Allocation concealment will be ensured, as the service will not release the randomization code until the patient has been recruited into the trial, which takes place after all baseline questionnaires and measurements have been completed.

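### The stated access to the randomisation list includes people who recruit and is not limited to past allocations, so it sits badly with the concealment claimed

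*Protocol article*

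**What the plan says.** Four sections of the protocol article bear on this.

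- **Sequence generation {16a}.** Allocation is 1:1 in permuted blocks with a "variable block size with a minimum of 4, a maximum of 8 and an increment of 2", stratified by centre and two age groups. "Randomization will be done by the research assistant of Reade". On access: "Randomization list will only be available to the local researcher of the rehabilitation centre, the executive investigator and principal investigator".
- **Concealment mechanism {16b}.** Concealment is said to be assured because "the service will not release the randomization code until the patient has been recruited into the trial", and recruitment in that sense comes after all baseline questionnaires and measurements.
- **Recruitment {15}.** For people who respond to a flyer (the inactive route), "The executive or principal investigator will then perform a pre-screening interview via telephone". Those found suitable are passed to a local research assistant. On the active route there is no telephone pre-screening.
- **Who will take informed consent? {26a}.** "The physical screening is carried out by the local investigator or trained research assistants". That visit covers reassessment of eligibility, explanation, consent and a check of muscle contraction. Then: "If these inclusion criteria have also been met, the participant will be included in the study". On timing: "After the baseline questionnaire is fully completed, the participant will be randomized to the intervention or control group".

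**The concern.** Concealment means that nobody who influences whether a candidate enters can know, or predict well, the next allocation. The access rule names two people who pre-screen and one role that seems to screen and consent. It does not say whether the list holds the generated sequence or only the allocations already released.

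This matters more here because participants and local staff know the arm, and several entry criteria leave room for judgement: how severe autonomic dysreflexia or a cognitive disorder is, whether prone lying is tolerated, whether the contraction on testing is adequate. Someone who expected a given arm next could, without intending to, let a higher-risk candidate through or hold one back. With about 50 participants per arm, a few such decisions could unbalance the risk of a pressure ulcer. The planned confounder adjustment reaches only measured factors, so the analysis could not be relied on to repair this.

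**Working it through.** The article gives no figure on this point, so the main check is to set the roles side by side.

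| Role | Has the list ({16a}) | Part in deciding entry | Overlap |
|---|---|---|---|
| Executive and principal investigators | Yes | Telephone pre-screening, inactive route only ({15}) | Explicit |
| Local researcher of the centre | Yes | Physical screening and consent, if this is the local investigator or research assistant of {26a} | Inferred; the article does not define the roles separately |
| Research assistant of Reade | Not named | Performs the randomisation | None stated |

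Access is therefore stated for people on the recruiting side, and the person who operates the randomisation is not named among those who have it. No section limits the list to allocations already made or separates its holders from screening.

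**What each reading would allow**

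*Reading A: the list shows upcoming allocations.* The next allocation in a stratum is then known with certainty.

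*Reading B: the list shows past allocations only.* A reader who knows the published block sizes can guess the arm that lags in the stratum, and guess at random when the arms are level. Inputs: 1:1 ratio and blocks of 4, 6 or 8 ({16a}). Assumption: the three sizes are equally likely, which the article does not state.

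Hand check for small strata:
- First participant: 0.5.
- Second participant: in a block of size b, the chance that the second differs from the first is (b/2)/(b−1). That is 2/3, 3/5 and 4/7 for b = 4, 6 and 8; mean (0.6667 + 0.6000 + 0.5714)/3 = 0.6127.
- Third participant: the same three values result. For b = 4, the first two agree with chance 1/3 and the third is then certain; otherwise it is a coin toss: 1/3 × 1 + 2/3 × 0.5 = 0.6667. For b = 6: 2/5 × 3/4 + 3/5 × 0.5 = 0.6000. For b = 8: 3/7 × 2/3 + 4/7 × 0.5 = 0.5714. Mean 0.6127.
- Stratum of 2: (0.5 + 0.6127)/2 = 0.556. Stratum of 3: (0.5 + 0.6127 + 0.6127)/3 = 0.575.

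Simulation of the same strategy (200,000 sequences per size):

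| Participants in stratum | Correct guesses |
|---|---|
| 2 | 55.6% |
| 3 | 57.5% |
| 4 | 62.6% |
| 6 | 64.8% |
| 13 | 66.0% |
| 25 | 67.0% |

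Eight centres by two age groups give up to 16 strata, so the mean is 100/16 ≈ 6 participants. The strata aged 70 and over may be smaller.

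**Timing.** {26a} puts randomisation after the baseline questionnaire; {16b} puts it after all baseline questionnaires and measurements. The second order satisfies the first. The shorter sentence is incomplete, but the two are compatible.

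**The case against.** The strongest reply is that the sections can be read together. {16b} is the operative statement: a web service holds the code until the participant is in. The access sentence restricts access to three roles, and Confidentiality {27} names the same three roles for personal data, which suggests a data-access rule. Who will be blinded {17a} leaves local assistants unblinded and excepts the principal investigator from the researchers who stay blinded. A log of completed allocations, held by people who must know them anyway, fits all of this.

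This stands in part. A reader might infer that enrolling staff can look up the next allocation, or that {16a} flatly contradicts {16b}. The text supports neither: it never says that the list shows upcoming allocations. But it never says the opposite, and the sentence stands in the section on generating the sequence, directly after the blocks and strata.

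Three further replies are fair:
- **Limited overlap.** It is explicit only for the two investigators and only on the inactive route. Local staff then reassess every criterion, and the information letter goes out at least 5 working days before screening, so a pre-screener has little control over which place in the sequence a candidate takes. This weakens the scope for steering, but a pre-screener still decides who goes forward.
- **Guessing without the list.** Unblinded local staff know their own centre's past allocations whatever the list shows. This is correct: the guessing rates above are not caused by list access at a site. Only the pre-screeners' view across centres is.
- **Timing.** A reader might infer that physical baseline measurements could be taken with the allocation known. {16b} rules that out, so this is a matter of wording.

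**Conclusion.** The point holds as a defect in a stated access rule. The rule gives a list of undefined content to two people who pre-screen and to a role that appears to screen and consent, and so undercuts the concealment that {16b} claims. It permits selection bias; nothing shows that bias would occur, and its effect on the primary result cannot be derived from the article.

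The size depends on what the list is. Certainty about the next allocation follows only under Reading A, which the article does not establish. Under Reading B, guesses are right about 56% to 67% of the time against 50%, and about 65% at the mean stratum size, assuming equally likely block sizes. Much of that exists at each centre anyway. What the access rule adds is any view of upcoming allocations and the central pre-screeners' view of past ones. The local overlap also rests on taking the local researcher to be the person who screens.

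**What to change.** 1. Amend {16a}: nobody who pre-screens, screens, takes consent or includes participants can see the sequence or any upcoming allocation. The web service releases one allocation at a time, after enrolment.
2. During recruitment, withhold the cumulative list by stratum from the investigators who pre-screen.
3. If the list means completed allocations only, say so.
4. As a clarification, align {26a} with {16b}: randomise after all baseline questionnaires and measurements.

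The cost is access settings in the web service and a few sentences. The two investigators lose their overview of allocations while recruitment runs. Some guessing by unblinded local staff from their own centre's past allocations remains, at about 56% to 66% correct for strata of 2 to 13 participants on the same block assumption.
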